### 2.7. Sample Size Calculation

The sample size will be estimated using power analysis from a two-sided Z test, adopted from Charan and Biswas [38], with a 1.5 design effect and a 10% nonresponse rate [39].

This will take into account the desired level of statistical significance, effect size, and expected variability.

The formula is as follows:$$n=\frac{2(Z_{\alpha /2}+Z_{\beta }{)}^{2}P(1-P)}{(P_{1}-P_{2}{)}^{2}}$$
where:

$Z_{\alpha /2}$ = $Z_{0.05/2}$ = $Z_{0.025}$ = 1.96 is the critical value (from the Z table) at type 1 error, which is the critical value for the chosen level of significance.

$Z_{\beta }$ = $Z_{0.20}$ = 0.842 is the critical value for the chosen power from the standard normal distribution at 80%.

$P_{1}$ = 71.5% is the estimated proportion of the population with the outcome of interest in the control group. This figure is derived by averaging the proportions observed in two previously related studies [24,39] examining one of the outcomes of interest, facility-based deliveries without intervention.

$P_{2}$ = 81.5% is the estimated proportion of the population with the outcome of interest in the intervention group. Like P1, this is also obtained by averaging proportions from the same two related studies [31,32], but in this case, focusing on facility-based delivery with intervention.

P = 76.5% is the pooled prevalence [prevalence in case group ${(P}_{1})$ + prevalence in control group ${(P}_{2})$]/2.

$P_{1}-P_{2}$ = −10% is the difference in the proportion of events in the two groups.

The sample size calculated using the power analysis and taking into consideration the design effect and nonresponse yielded 465 participants in each of the groups (control (465) and treatment (465)) at 80% power and at the 5% level of significance.

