## Abstract

Background: About 287,000 women died globally during their pregnancy journey in 2020, yet most of these deaths could have been prevented. In Uganda, studies show that using Community Health Worker (CHW) visits to households with a pregnant woman can support the prevention of adverse maternal and neonatal outcomes. One such intervention is through the timed and targeted counselling (ttC) approach, where CHWs deliver tailored messages to mothers and their male caregivers at key stages of pregnancy. This study aims to evaluate the impact of the ttC approach on maternal health in Northern Uganda. The main outcomes include antenatal care attendance, advised place of delivery, and postnatal care visit. Methods: We will employ a cross-sectional quasi-experimental design, with retrospective data to compare an intervention group (where ttC is implemented) to a control group (without intervention) using the propensity score matching (PSM) technique applying a 1:1 ratio with a caliper width of 20% of the standard deviation to estimate the average treatment effects. Adjusted odds ratios after generating matched pairs will be reported with 95% confidence intervals with Rosenbaum sensitivity analysis carried out for robustness. Discussion: These findings can be used to modify the implementation of the ttC approach, thereby enhancing its efficiency and effectiveness.

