### 2.8. Sampling Procedure

To reach the above calculated sample size, a three-stage sampling procedure will be used. First, a simple random sampling within Oyam district will be conducted to select one subcounty where the treatment (ttC implementation) was applied (Aber subcounty) and another where it was not (Otwal subcounty). This random selection ensured that both the intervention and the non-intervention areas were chosen in an unbiased manner.

In the second stage, stratified sampling will be done within the two subcounties to provide the sampling unit, being women of reproductive age (between 18 and 49 years) who have given birth to babies between 2 and 12 months of age. For internal homogeneity within each subcounty, two strata will be formed, one from each subcounty. A total of 930 mothers will be sampled from the 2231 eligible mothers (465 from the 876 available in the intervention subcounty and 465 from the 1355 available in the control subcounty) as per the sample size calculation above. 

Finally, in the third stage, a systematic sampling method will be applied to randomly select the 930 mothers from an alphabetically compiled list of eligible mothers. A random starting point and a fixed interval will be applied to select participants 465 participants from each subcounty. This process ensures an equal and unbiased representative sample for later generalisation of findings to other similar settings. The flow of this sampling process is shown in Figure 2 below.

By justifying and implementing this comprehensive sampling methodology, the study will aim to enhance the reliability and validity of the research findings.

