### 2.10. Data Analysis

After the data have been cleaned, they will be exported to STATA for analysis and Excel for better visualization. Descriptive and summary statistics will be drawn using the frequencies, measures of central tendency, and dispersion with proportions to provide a descriptive analysis of the context.

There will be cross tabulation of the chosen covariates (education level, birth parity, income, and age) with the intervention (ttC) to obtain their frequency distribution among the treatment and control arms together with the p-values. A logistic regression of the intervention and the covariates will be used to generate the propensity scores. A caliper width at the 20% of the standard deviation will be used for matching participants using the greedy nearest neighbor method in order to get the average treatment effects and the impact of the ttC intervention on the outcomes ANC, PoD, and PNC [40,41].

**
Sensitivity Analysis
**

Sensitivity analysis will be performed using the Rosenbaum bounds to test the conditional on the unobserved variables, and that the study is free from hidden bias [42]. This will use the rbounds commands in STATA version 14 ranging from 1 to 1.5 with an increment of 0.05. The gamma value will show whether hidden bias is present, as well as the robustness of the results to this potential hidden bias [43]. The sensitivity analysis results for the outcomes will demonstrate whether the treatment effects remain significant and robust to unobserved confounding, even in the presence of hidden bias. This should be across different gamma levels and confidence intervals to ensure the reliability and validity of treatment effects, therefore indicating stability [42,43].

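### The 80% power at 465 per group makes no allowance for mothers lost to 1:1 caliper matching, so it does not describe the planned analysis

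*Protocol article*

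**What the plan says.** **Sample size (protocol article, section 2.7).** "The sample size will be estimated using power analysis from a two-sided Z test", "with a 1.5 design effect and a 10% nonresponse rate". The inputs are facility delivery of 71.5% in the control group and 81.5% in the intervention group, a pooled proportion of 76.5%, and normal quantiles of 1.96 and 0.842. The result "yielded 465 participants in each of the groups (control (465) and treatment (465)) at 80% power and at the 5% level of significance". Design effect and nonresponse are the only adjustments named.

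**Sampling (section 2.8).** Exactly 465 mothers are drawn from each subcounty, out of 876 in Aber and 1355 in Otwal.

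**Analysis (Abstract and section 2.10).** The Abstract describes propensity score matching "applying a 1:1 ratio with a caliper width of 20% of the standard deviation", with odds ratios reported once the pairs have been formed. Section 2.10 repeats the method: "A caliper width at the 20% of the standard deviation will be used for matching participants using the greedy nearest neighbor method". Neither place gives an expected match rate or says whether a control may be used more than once.

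**The concern.** A caliper exists to exclude mothers who have no close counterpart. In many matched studies this costs little, because the control pool is several times larger than the treated pool. Here the pools are equal, so matching without replacement cannot draw on a reserve, and the analysed number falls with every failed match.

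Section 2.7 therefore gives the power of an unmatched comparison of all respondents, and the trial reports a different analysis. If the matched analysis has 70 to 75% power, the chance of missing a true 10-point difference in facility delivery is between one in four and about three in ten, not one in five. A reader relying on the printed 80% could then read too much into a null result.

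**Working it through.** **1. Reproduce the stated figure.** Inputs are from section 2.7.

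- n = 2 × (1.96 + 0.842)² × 0.765 × 0.235 / 0.10² = 282.3 per group
- Design effect: 282.3 × 1.5 = 423.4
- Nonresponse as × 1.10: 423.4 × 1.10 = 465.8 (465.3 if 282 is carried forward)

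The printed 465 is reproduced, with nonresponse applied as a 10% addition.

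**2. Nonresponse applied as a loss.** If 10% do not respond, the number to sample is 423.4 / 0.90 = 470.5, so 471. Conversely, 465 × 0.90 = 418.5 respondents, slightly fewer than the 423.4 required.

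**3. Power of the matched analysis.** Let m be the share of respondents matched. The effective number per group is 465 × 0.90 × m / 1.5 = 279m, and

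power = Φ(0.10 / √(2 × 0.765 × 0.235 / 279m) − 1.96).

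| Share matched (assumed) | Mothers per group | Effective n | Power |
|---|---|---|---|
| 100% | 418.5 | 279.0 | 79.55% |
| 95% | 397.6 | 265.1 | 77.5% |
| 90% | 376.7 | 251.1 | 75.3% |
| 80% | 334.8 | 223.2 | 70.2% |
| 70% | 293.0 | 195.3 | 64.5% |

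With the unpooled variance under the alternative, the first row is 79.7%, so the choice of formula hardly matters. Power falls more than 2 points below 80% once about 4% of respondents are unmatched (77.9% at m = 0.96).

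**4. Plausible match rates.** The protocol gives none, so they were simulated: 418 v 418, greedy nearest neighbour, without replacement, caliper 0.2 SD, normally distributed score, 200 replicates.

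| Standardised difference in the score (assumed) | Matched | Power |
|---|---|---|
| 0 | about 92% | 76% |
| 0.25 | about 88% | 74% |
| 0.50 | about 80% | 70% |
| 0.75 | about 71% | 65% |

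A second simulation estimated the score from categorical covariates, closer to Table 2 but with assumed distributions. It matched about 91% with no true imbalance and about 80% at a standardised difference near 0.46, which gives about 76% and 70% power.

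**5. Dependence on the design effect.** With a design effect of 1 instead of 1.5, the same formula gives 90%, 86% and 81% at 90%, 80% and 70% matched. Power stays at or above 80% down to 282.3 / 418.5 = 67.5% matched.

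**The case against.** **The nonresponse slip is trivial.** This stands. It amounts to 6 mothers per group and, with all respondents matched, less than half a point of power. A reader might infer from step 1 that the calculation is broken. It is not: 465 follows from the stated inputs, and the slip alone would not justify changing the claim.

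**The size of the loss is assumed.** This stands in part. The protocol gives neither a match rate nor covariate distributions, only four covariates enter the score, and section 2.2 says the subcounties were chosen for their similarity. It would be tempting to call 65 to 76% the realistic range, but the lower end needs a standardised difference of about 0.75, which nothing in the document supports. What does not fall away is the loss at small imbalance: about 8 to 12% of respondents go unmatched in the simulation at differences of 0 to 0.25.

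**The shortfall rests on the 1.5.** This also stands as a condition. Section 2.8 draws individual mothers from a list, with no village or health-worker stage, and step 5 shows ample power without the design effect. But 1.5 is the protocol's own input, and the 80% was claimed with it. Outcomes may also cluster by community health worker.

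**Replacement is not specified.** Correct. Allowing a control to be reused would retain more treated mothers, but repeated controls add less information, and section 2.7 does not account for that either.

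**Sampling interval.** Section 2.8 says "A random starting point and a fixed interval will be applied", and a reader might infer whole-number intervals, giving 876/2 = 438 and 1355/3, about 452, instead of 465. The text does not say whole-number. Intervals of 876/465 = 1.884 and 1355/465 = 2.914 are fixed and yield 465, so there is no error here.

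**Conclusion.** The point holds as a mismatch between the power statement and the analysis. Because the same article gives both the power figure and the matching method, this is not detail left to an analysis plan.

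Under the protocol's own inputs, 465 per group gives marginally under 80% only if every respondent is matched. It gives about 75% at 90% matched and 70% at 80% matched. The figures rest on four assumptions: 10% nonresponse occurs, the design effect of 1.5 is needed in full, matching is without replacement, and matched pairs are about as precise as independent groups of the same size.

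The document does not support a firm figure for the loss, nor a claim that power will be as low as 65%. What can be said is that no allowance was made, and that a loss of several points is likely even with well-balanced groups if the design effect is right.

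**What to change.** In section 2.7:

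- State 471 per group as the number to sample for the given assumptions before matching.
- Give the power of the matched analysis at 465 sampled over a stated range of match rates, for example 75%, 70% and 64% at 90%, 80% and 70% matched.
- Say whether matching is with or without replacement.

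A propensity-score weighted analysis of all respondents could be added, as a sensitivity analysis at most. Making it primary could change the target population, which this point does not require.

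The cost is a few restated lines and a less favourable power statement. Enlarging the sample is optional. The lists would allow it, at 470.5 / 0.90 = 523 per group for a 10% matching loss or 470.5 / 0.80 = 589 for 20%, but it adds fieldwork and is not needed to correct the claim.

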### 2.8. Sampling Procedure

To reach the above calculated sample size, a three-stage sampling procedure will be used. First, a simple random sampling within Oyam district will be conducted to select one subcounty where the treatment (ttC implementation) was applied (Aber subcounty) and another where it was not (Otwal subcounty). This random selection ensured that both the intervention and the non-intervention areas were chosen in an unbiased manner.

In the second stage, stratified sampling will be done within the two subcounties to provide the sampling unit, being women of reproductive age (between 18 and 49 years) who have given birth to babies between 2 and 12 months of age. For internal homogeneity within each subcounty, two strata will be formed, one from each subcounty. A total of 930 mothers will be sampled from the 2231 eligible mothers (465 from the 876 available in the intervention subcounty and 465 from the 1355 available in the control subcounty) as per the sample size calculation above. 

Finally, in the third stage, a systematic sampling method will be applied to randomly select the 930 mothers from an alphabetically compiled list of eligible mothers. A random starting point and a fixed interval will be applied to select participants 465 participants from each subcounty. This process ensures an equal and unbiased representative sample for later generalisation of findings to other similar settings. The flow of this sampling process is shown in Figure 2 below.

By justifying and implementing this comprehensive sampling methodology, the study will aim to enhance the reliability and validity of the research findings.

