### 2.2. Research Area

The study area will be the northern region of Uganda, specifically the Oyam district, which was selected because ttC is implemented in the Aber subcounty of the district. Northern Uganda in particular is an important region for studying maternal health due to its high poverty rates [32], cultural diversity, limited healthcare access, poor health outcomes, and the presence of conflict-affected individuals [33].

Taking the Oyam district as the sampling frame, two subcounties, Aber and Otwal, are chosen for reaching out to mothers who would have given birth within the past 2–12 months. Aber is the treatment subcounty, and Otwal is the control subcounty because ttC is implemented in the former, but not in the latter. However, the two subcounties of Aber and Otwal were chosen because they are located within the same district and therefore have similar health challenges, such as limited health care access and similar poverty situations in the conflict-affected region [33]. Approximately 18.3% of the population in Aber and 22.3% of the population in Otwal aged 10–19 years have ever been married [34]. Furthermore, in 2021, these two subcounties, among others in Oyam district, had one of the highest teenage pregnancy rates in Uganda [35,36]. Factors mentioned by these new young mothers for the high rate of teenage pregnancy include a lack of knowledge of the ovulation period, inadequate sex education, and social norms that prevent parents from talking to their children about sex education [36]. Significantly, both subcounties are chosen because they do not share borders with each other; thus, limited spillovers are expected from the treatment subcounty to the control subcounty.

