### Strengths and Limitations

This study’s main limitation is the use of a cross-sectional dataset to experiment with an intervention. However, propensity score matching will be used as an alternative to a randomised trial by eliminating the bias due to confounding, and thereby ably applying causal inference for the results [30]. Another limitation would be the several unmeasured confounders which would improve precision if included in the study. This will be mitigated by using sensitivity analysis to sow robustness of the results to these unmeasured confounders [43]. There may be response bias due to self-reporting, which may affect the information gathered. This limitation will be addressed by providing confidentiality assurance to the study participants to allow them to answer more truthfully. Finally, spillover effects will be mitigated by having distant subcounties that do not share borders.

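### Section 2.8 calls the choice of Aber and Otwal random and unbiased, and the limitations say matching eliminates confounding; with one purposively chosen subcounty per arm, neither claim holds

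*Protocol article*

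**What the plan says.** **How the areas were chosen.** Section 2.8 describes a first sampling stage in which one ttC and one non-ttC subcounty are drawn at random within Oyam, and it already names Aber and Otwal as the result. It concludes: "This random selection ensured that both the intervention and the non-intervention areas were chosen in an unbiased manner".

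Section 2.2 gives reasons of a different kind. Of the district it says: "which was selected because ttC is implemented in the Aber subcounty of the district". Of the subcounties it says "the two subcounties of Aber and Otwal were chosen because they are located within the same district" and, to limit spillover, "both subcounties are chosen because they do not share borders with each other". The arms follow from where the programme runs: "Aber is the treatment subcounty, and Otwal is the control subcounty because ttC is implemented in the former, but not in the latter".

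**What matching is said to do.** Sections 2.1 and 2.10 build the propensity score from education level, parity, income and age. Strengths and Limitations states that "propensity score matching will be used as an alternative to a randomised trial by eliminating the bias due to confounding". The same paragraph admits several unmeasured confounders, describes them as a matter of precision, and relies on sensitivity analysis to deal with them. Section 2.10 specifies Rosenbaum bounds with gamma from 1 to 1.5 in steps of 0.05, and gives as one purpose testing that hidden bias is absent. Having a single subcounty in each arm is not listed as a limitation.

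**The concern.** Two separate problems meet here.

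The first is a contradiction. Areas chosen for stated characteristics are not a simple random draw, and the claim of unbiasedness in section 2.8 rests on the draw.

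The second is a limit of the design that the text denies. With one subcounty per arm, whatever differs between Aber and Otwal other than ttC differs between the arms as well. Matching mothers on four individual or household characteristics does not touch such differences.

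All three specific objectives are worded as the impact of ttC, and section 2.8 looks ahead to generalising the findings to similar settings. Without the right caveat, an adjusted difference that is partly or wholly due to area could be read as the effect of the counselling package. Sampling more mothers in the same two subcounties would not help.

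**Working it through.** **1. Selection, side by side.** Section 2.8: random draw, hence unbiased. Section 2.2: district chosen because ttC runs in Aber; subcounties chosen for being in the same district and for having no common border. Even a genuine draw of one area of each type would not make the two areas comparable, because ttC was not allocated to subcounties at random.

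**2. Aliasing.** Section 2.4 takes the 876 treatment mothers from one subcounty and the 1355 control mothers from the other. Section 2.3 says control CHWs did not use ttC. Two areas less two arms leaves 2 − 2 = 0 degrees of freedom for between-area variation, so an area effect can be neither estimated nor removed. No area-level covariate is among the matching variables.

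**3. The plan's own sample size reproduces.** Inputs from section 2.7: P1 = 0.715, P2 = 0.815, P = 0.765, Z values 1.96 and 0.842, design effect 1.5, nonresponse 10%.
- n = 2 × (1.96 + 0.842)² × 0.765 × 0.235 / 0.10² = 282.3
- 282.3 × 1.5 = 423.4
- 423.4 × 1.10 = 465.8, against the stated 465

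The arithmetic is not at fault.

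**4. What the 1.5 design effect could absorb.** If each subcounty is one cluster of m = 465, then 1 + (m − 1) × ICC = 1.5 gives ICC = 0.5/464 = 0.0011. The allowance covers only a very small subcounty effect.

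**5. Illustration of size.** Let τ be the between-subcounty SD in facility delivery that remains after matching. The documents give no value, so τ is an assumption shown over a range. Assume also that 465 × 0.9 = 418.5 mothers per arm respond and are all matched, and that the test allows for the 1.5 design effect.
- SE = √(2 × 0.765 × 0.235 × 1.5 / 418.5) = 0.0359, or 3.6 percentage points
- With no ttC effect, the Aber–Otwal difference has variance SE² + 2τ²
- Chance of p < 0.05 = 2 × [1 − Φ(1.96 × SE / √(SE² + 2τ²))]

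| τ (points) | √(SE² + 2τ²) | critical value on the true scale | chance of a significant result |
|---|---|---|---|
| 2 | 0.0457 | 1.54 | 12% |
| 3 | 0.0556 | 1.27 | 21% |
| 5 | 0.0793 | 0.89 | 37% |

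**6. What the bounds can show.** Gamma limits how far an unmeasured factor may shift the odds of treatment within a matched pair. A factor that coincides with subcounty also coincides with the arm, so its association with treatment is not confined to 1.5. A result that stays significant up to 1.5 has withstood that much hidden bias; it has not been shown to be free of it.

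**The case against.** The plan does not ignore hidden bias. It calls the design quasi-experimental, names the cross-sectional data as its main limitation, admits unmeasured confounders and plans Rosenbaum bounds. A reader might infer from this point that the plan recognises no residual confounding; the documents do not support that. But the admission treats unmeasured confounders as a loss of precision, sits beside a claim that confounding bias is eliminated, and never mentions one area per arm.

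Section 2.2 could be read as eligibility limits applied before a draw. The documents do not say how many subcounties qualified, so purposive selection is the natural reading of the stated reasons, not something recorded outright. The objection reaches only the contradiction: the aliasing is the same after a real draw.

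Section 2.9 and Table 2 define ttC by the mother's report of having received it, so the analysed contrast may not be exactly Aber against Otwal. That stands as a caution on wording. It does not separate ttC from area, because sections 2.3 and 2.4 tie access to Aber; discordant reports would be non-receipt or misclassification.

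Two subcounties in one district may well be similar, and a single treated area is a constraint of evaluating an existing programme. Both are fair. Neither shows that area differences are absent, and neither supports the word eliminating.

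The percentages depend on an assumed τ, on the 1.5 being used in the test (section 2.10 does not say so) and on no mothers being lost to the caliper. This stands in full.

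**Conclusion.** The point holds as a fault in what the text claims. Section 2.8 attributes to the choice of areas a randomness that section 2.2 contradicts. Strengths and Limitations attributes to matching a property that it cannot have with one subcounty per arm and four mother-level or household covariates. The bounds in section 2.10 do not fill the gap.

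A reader might go further and infer that this trial's type I error is between 12% and 37%, or that Aber and Otwal do differ in ways that bias the result. The documents support neither: they give no between-area variation and no evidence of an actual area gap. The figures only illustrate that a modest residual area difference would matter against the planned 10-point effect. Nor does it follow that the study must be redesigned or that a further analysis is required; the necessary correction is to the wording of the claims.

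**What to change.** **Needed, text only.**
- Section 2.8: delete the random-selection and unbiasedness wording for the subcounties, and state that Aber and Otwal were chosen purposively, for the reasons in section 2.2.
- Strengths and Limitations: replace the claim of eliminating confounding bias with *reducing bias from the measured mother-level covariates*. Name one subcounty per arm as a main limitation, and state that the estimated ttC effect may include Aber–Otwal area differences that matching cannot remove.
- Section 2.10: drop the statement that the bounds test for freedom from hidden bias, and say that they show how much hidden bias a result would withstand.

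The cost is a few sentences and more modest causal wording.

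**Optional and exploratory.** If the ttC start date in Aber is known (the article does not give it), ask mothers with parity of 2 or more about a birth before ttC began, using the same ANC, PoD and PNC definitions as Table 2, and report the pre-ttC gap between the subcounties. The cost is a few questionnaire items and longer recall. State the limits: any comparison of change over time needs parallel trends, changes specific to one area over time still cannot be separated from ttC, and first-time mothers are excluded.
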